## Abstract

**Background:**

Cannabis is the most widely used illicit substance. Various countries have legalized cannabis for recreational use. Evidence on the health effects of cannabis regulation remains unclear and is mainly based on observational studies. To date, there is no randomized controlled study evaluating the impact of cannabis regulation for recreational use compared to the illicit market on relevant health indicators. The present study (“Weed Care”) is the first to evaluate the impact of regulated cannabis access in pharmacies versus a waiting list control group representing the illicit market on problematic cannabis use as well as on mental and physical health.

**Methods:**

The study is divided into two parts—a randomized controlled study of 6 months followed by an observational study of 2 years. Participants (*N* = 374) are randomly assigned to either the experimental group with access to legal cannabis in pharmacies or to the waiting list control group representing the current legal framework in Switzerland, namely the illicit market. After 6 months, all participants will have access to legal cannabis for the following 2 years (observational study). The primary outcome is problematic cannabis use as measured with the Cannabis Use Disorders Identification Test-Revised (CUDIT-R). Secondary outcomes are cannabis use patterns, mental disorders (e.g., depression, anxiety, and psychosis) and physical health (e.g., respiratory symptoms). Primary and secondary outcomes will be assessed online every 6 months. The study is approved by the responsible ethics committee as well as by the Swiss Federal Office of Public Health.

**Discussion:**

Findings from this study may provide a scientific basis for future discussions about addiction medicine and cannabis policy in Switzerland.

**Clinical Trial Registration:**

ClinicalTrials.gov (NCT05522205). https://clinicaltrials.gov/ct2/show/NCT05522205

## Introduction

Cannabis has been an illicit substance in countries that signed the UN Single Convention for more than 50 years. Nevertheless, cannabis is the most commonly used illicit substance globally. In 2020, the United Nations estimated that 209 million or 4% of persons of the global adult population had used cannabis in the previous year (1). The last-year prevalence of the European adult population is 22.2 million or 7.7% (2). Switzerland has one of the highest national prevalence rates of cannabis use in Europe. Whereas the lifetime prevalence for European adult population is 27.3%, the lifetime prevalence for the Swiss adult population is 34% (3). Approximately 4% of the Swiss population used cannabis in the past-month (3).

These prevalence rates suggest that cannabis prohibition has not been able to sustainably reduce cannabis use. In contrast, prohibition is associated with high health and social costs due to unsafe product quality, stigmatization and criminalization of users as well as access barriers to harm reduction, prevention, and treatment (4, 5). Furthermore, cannabis causes less societal and individual harm compared to illicit opioids and stimulants (6) or legal drugs such as alcohol and tobacco (7, 8). The comparatively high number of users, the modest harms of cannabis use, as well as the high costs of its prohibition have led to increased public discourse reconsidering prohibition and prompting alternative cannabis regulation models.

Besides strict prohibition, the opposite pole of the legislative spectrum—free commercial market—is equally associated with increased public health costs, because industry is interested in promoting cannabis use (9). In contrast, the middle-ground regulation may minimize the adverse effects of both extremes. This could be achieved by implementing policies to improve public health and safety, to protect minors, as well as to reduce crime (9, 10). These policies may include, e.g., pricing according to product potency, a governmental monopoly on production and sales, restriction of advertisement, minimum age, health education on safer use, prevention programs, and treatment-referrals (11).

Various states have introduced legal cannabis laws for recreational use and further countries propose to legalize cannabis in the near future. The implemented regulatory models vary widely. In particular, since 2012 over a dozen US states have implemented a commercial cannabis model similar to the alcohol and tobacco regulations (12). Canada followed suit in 2018 with a focus on public health (13), while in Uruguay cannabis is strictly regulated and controlled by the government since 2013 (14). Given the general shift in cannabis legislation—away from prohibition toward regulation—knowing the effects of these policies on cannabis use patterns as well as on mental and physical health is paramount for clinicians and policymakers alike. However, evidence for public health from available observational studies is inconclusive.

Recreational cannabis legalization in US states has been associated with an increased frequency of cannabis use among adults (15, 16). Among adolescents and young adults (< 21 years), there was no association between cannabis legalization and cannabis use (15, 17–19). In Uruguay, the legalization of recreational cannabis was not associated with past-month- and past-year-prevalence among young adults (18–21 years); however, it was associated with a transitory increase in risky and more frequent use in young adults that decreased thereafter (20). The cannabis regulation in Canada was associated with an increased 3-month prevalence among adults (> 25 years), but not related with increased frequency of use (21, 22). Additionally, a shift in mode of administration toward lower-risk methods has been observed. Specifically, cannabis users reported less cannabis smoking, increased vaporizing, and consumption of edibles following cannabis legalization (21).

To assess the public health impacts of recreational cannabis regulation, previous studies predominantly evaluated the prevalence and frequency of cannabis use (23). However, these outcomes are of limited clinical significance since the majority of cannabis users are low-risk users and do not suffer from adverse health outcomes related to their use (24). Nonetheless, between 10 and 30% of those, who use cannabis, do fulfill the criteria for a cannabis use disorder (25–28). As cannabis use disorders substantially contribute to the global disease burden (29), investigating the impact of legalization on cannabis use disorder may be of greater concern for public health.

Additionally, not only cannabis use, but also comorbid mental and physical health indicators are of major interest for public health and drug policy reforms (23). Cannabis use disorder has been associated with comorbid psychiatric disorders (30, 31), in particular with an increased risk of use disorders of other substances, psychosis (32, 33), anxiety (34), and depression (35, 36). Whereas extensive evidence has shown that frequent use of potent cannabis is related to an increased risk of psychosis, the evidence for depression and anxiety is less clear (37–39). However, a causal relation was not established in these studies. Thus, it remains unclear whether the increased risk of mental disorders is attributable to cannabis use or other confounding factors. Furthermore, the relation between cannabis use and physical health is also uncertain. Chronic bronchitis is the most consistently found adverse effect of cannabis smoking (40, 41). In contrast to the adverse health effects of cannabis use, there is additional growing evidence evaluating the beneficial health effects of medical cannabis. Medical cannabis has been associated with improvements of symptoms of mental disorders, including anxiety, schizophrenia, and sleep (42, 43). Further, low-to-moderate evidence supports the treatment of a range of physical conditions, including chronic pain, nausea, and vomiting caused by chemotherapy, and some treatment resistant epilepsies (44, 45). However, evidence on the impact of recreational cannabis legalization on comorbid mental and physical health outcomes in cannabis users is rare. One epidemiological study has shown that cannabis laws for medical use in the US are associated with reduced mental health problems (46). Research on the impacts of recreational cannabis laws on mental and physical health indicators in cannabis users is yet lacking.

To our knowledge, there is no randomized controlled study evaluating the effects of recreational cannabis legalization compared to the illicit market on relevant health outcomes. Available evidence is based on observational studies, including pre-post-legalization comparisons or comparisons between states with recreational cannabis regulation and states without. However, these study designs are not able to distinguish between secular trends and changes due to cannabis regulation and thus, causality remains unclear (47). The aim of the present randomized controlled study is to investigate the effects of cannabis regulation for recreational purposes compared to the illicit market on problematic cannabis use, mental disorders, and physical health. Although cannabis for recreational use is prohibited in Switzerland, scientific studies on recreational cannabis are allowed since 2021 (48). Hence, Switzerland offers a unique opportunity to gain scientific knowledge about alternative cannabis regulation approaches. We hypothesize that regulated cannabis access in pharmacies will reduce problematic cannabis use as within a regulated approach several conditions are available to facilitate lower-risk use and treatment. Furthermore, we hypothesize that regulated cannabis access will improve mental and physical health outcomes.

Moreover, the effects of chronic cannabis use on epigenetic DNA-expression regulation are not yet fully understood. Its mechanisms may provide explanations for the development of cannabis use disorder and cannabis withdrawal syndrome, as well as emotion-regulating effects of cannabis use. To date, an association between cannabis use and the expression of neurotrophic growth factors (49, 50) as well as changes in the hypothalamic–pituitary–adrenal (HPA) axis (51) have been observed. The Pro-opiomelanocortin (POMC) and NR3C1 genes play an important role in the regulation of the HPA axis, through which the release of stress hormones like adrenocorticotropin (ACTH) and cortisol occurs. The NR3C1 gene encodes the glucocorticoid receptor to which glucocorticoids such as dexamethasone bind and is essential for further signal transduction (52). POMC is a hormone precursor of interest, as it is susceptible to epigenetic regulation through DNA methylation as well (53). In patients with alcohol and opioid dependence, epigenetic gene express regulation mechanisms are associated with craving symptoms (54, 55). A pilot study showed a significant increase in POMC methylation in opioid-dependent patients following heroin injection (52). The neurotrophic growth factor brain-derived neurotrophic factor (BDNF) is associated with central dopamine release. Hence, an alteration in BDNF expression may be related to the reward effects and dependence potential of psychotropic substances (56). In the context of neurocognitive performance, as well as the development of substance-related dependence disorders, nerve growth factor (NGF), vascular endothelial growth factor-A (VEGF-A), and glial cell line-derived neurotrophic factor (GDNF) have been investigated in addition to BDNF (52, 57–59). However, in connection with cannabis use, the epigenetic regulation of these genes has so far been insufficiently studied and research on non-clinical populations of cannabis users is scarce.

## Methods

### Design

The study “Weed Care” is designed as a randomized, controlled, unblinded superiority trial with two parallel groups. Participants will be randomized to the experimental group with legal cannabis access in pharmacies or to the waiting list control group representing the illicit market. The primary endpoint is 6 months of regulated cannabis access. After 6 months, an observational study of 2 years will follow. During this time, both groups will have access to cannabis in pharmacies. This monocenter study will be conducted in the canton Basel-Stadt in Switzerland. The study has been approved by the local ethics committee “Ethikkommission Nordwest- und Zentralschweiz” (EKNZ) as well as by the Swiss Federal Office of Public Health. Furthermore, the study is designed in agreement with the Declaration of Helsinki, the ICH-GCP guidelines, and the Swiss law, notably the amendment of the Federal Act on Narcotics and Psychotropic Substances. The latter defines certain conditions for scientific studies with recreational cannabis such as minimum age of participants and maximum tetrahydrocannabinol (THC-) content (48).

### Eligibility criteria

Participants must provide written, informed consent before any study procedures occur. Eligibility criteria are checked by the study physician. Participants eligible for the study must comply with all of the following inclusion criteria:

Minimum age of 18 yearsCannabis use at least once per month during the last 6 months (including a positive THC-urine sample)Sufficient German language skillsResidence in Basel-StadtInternet access in order to answer online-questionnaires.

Exclusion criteria include:

Current pregnancy or breast feedingCurrent inpatient psychiatric treatmentAcute psychosisAcute suicidalitySevere cognitive impairment that does not allow to understand the study information nor to follow the study procedureAny intention to move away from Basel-Stadt within the next 12 months.

### Recruitment

A media conference in September 2022 informed the public about the current study. From this point on, interested persons were able to register online. After online registration, potential participants are contacted by phone for a first screening by the study nurse. Following, they are invited for a face-to-face interview with the study physician. In this interview, detailed information about the study is provided and written informed consent is obtained following the evaluation of inclusion/exclusion criteria. Individuals suitable for participation are randomly assigned to the experimental or control group. Furthermore, each participant will be asked to provide a blood sample. Recruitment has begun in September 2022 and will last until the required number of participants (*N* = 374) is reached, but no longer than 1 year.

### Participant timeline

Figure 1 shows the participant flow through the study. Legal cannabis access in pharmacies started on January 30, 2023. Both groups—the experimental as well as the control group—were invited to answer the baseline-survey two weeks prior to cannabis access (see Table 1). Follow-up assessments, using the full battery, will be collected every 6 months from baseline (at 6, 12, 18, 24, and 30 months) with a total of five main follow-up assessments. Additionally, short follow-up assessments are conducted every 2 months (at 2, 4, 8, 10, 14, 16, 20, 22, 26, and 28 months) with a total of ten short follow-up assessments. Main assessments lasts approximately 30 min, short assessments 10 min. Participants are required to answer the main assessments within 2 weeks, in order to buy cannabis in pharmacies. If they do not answer the questionnaires, they will be blocked.

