### Outcomes

Table 1 provides an overview of all measures and time points when they are assessed in the study. All questionnaires are administered in German and all available German versions of questionnaires are used. Additionally, all measurements are self-reported and assessed online.

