### Statistical methods

Descriptive statistics will be reported for sociodemographic and baseline characteristics. For the analysis of the primary outcome, analysis of covariance will be used (82). This model includes CUDIT-R mean after 6 months as dependent variable and the study group (experimental, control group) and the CUDIT-R mean at baseline as independent variable. Linear mixed models will be conducted for the analyses of the secondary outcomes in order to evaluate between-person and within-person differences during the 2 years of regulated cannabis access. Additionally, potential effect modification will be analyzed (gender, age, education, and cannabis consumption motives). Data will be analyzed according to the intention-to-treat-principle and thus (82), all patients being enrolled in the study and answered the baseline survey will be included.

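### The primary analysis adjusts for, and selects on, a self-reported baseline CUDIT-R that is collected after randomisation in an unblinded trial

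*Protocol article*

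**What the plan says.** Five statements in the protocol article bear on this point.

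- **Design:** the study is a "randomized, controlled, unblinded superiority trial with two parallel groups".
- **Recruitment:** after interview and consent, "Individuals suitable for participation are randomly assigned to the experimental or control group". The section also states that "Recruitment has begun in September 2022" and allows up to one year for it.
- **Participant timeline:** "Legal cannabis access in pharmacies started on January 30, 2023". Both groups, each named as such, "were invited to answer the baseline-survey two weeks prior to cannabis access".
- **Outcomes:** "all measurements are self-reported and assessed online".
- **Statistical methods:** the primary ANCOVA takes month-6 CUDIT-R as the outcome, with study group and "the CUDIT-R mean at baseline as independent variable". The intention-to-treat set consists of those enrolled who also completed the baseline survey.

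The article describes no CUDIT-R measurement before randomisation. It does not say when participants learned their arm.

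**The concern.** ANCOVA on a baseline score gives an unbiased treatment comparison in a randomised trial because the baseline cannot depend on allocation, so any baseline difference between arms is chance. A score collected after allocation, from people who may know their arm, does not carry that guarantee. If allocation changes the answers, the model treats the change as chance imbalance and adjusts for it.

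The article itself gives reasons why answers might differ by arm. Limitations names social desirability and expects that controls may not want to wait. Interventions says that marked deterioration in the online assessments prompts the study physician to review whether access should continue, which may matter more to someone about to receive access than to someone on the waiting list.

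The second route is selection. Because answering the survey is a condition for analysis and the survey follows allocation, non-response that differs by arm removes randomised people from the primary comparison.

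**Working it through.** **Sequence.** Recruitment and random assignment run from September 2022. Two weeks before January 30, 2023 is January 16, 2023. For the earliest recruits the survey therefore follows allocation by up to about four months. The timeline addresses the survey to two groups that already exist, so the order on the page is randomisation, then baseline.

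**The plan's sample size, to obtain an SD.** Inputs from Sample size: difference 2 points, power 0.8, alpha 0.05, dropout 20%, 187 per group. No SD or sidedness is given. Taking a two-sided test:

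- n per arm = 2 × (1.960 + 0.842)² × SD² / 2²
- SD 6.15 gives n = 149; 149 / 0.8 = 186.25, rounded up to 187; 2 × 187 = 374.
- Solving for exactly 149 gives SD = 6.16. A one-sided test would need 6.94.

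The dropout inflation is consistent. The SD of 6.16 is back-solved, not stated.

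**Bias.** Write differences as experimental minus control. ANCOVA gives

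adjusted difference = month-6 difference − slope × baseline difference.

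With no true effect, and allocation-induced shifts in that difference of s0 at baseline and s6 at month 6,

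net bias = s6 − slope × s0.

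**Baseline-only shift (s6 = 0).** Absolute bias b = slope × |s0|. With equal SD at both times, SE = 6.16 × √(1 − slope²) × √(2/149), and two-sided type I error = 1 − Φ(1.96 − b/SE) + Φ(−1.96 − b/SE). The slope is not in the article; 0.4 to 0.8 is an assumed range.

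| Assumed slope | SE | 0.5-point shift: bias, type I error | 1-point shift: bias, type I error |
|---|---|---|---|
| 0.4 | 0.65 | 0.2, 6% | 0.4, 9% |
| 0.6 | 0.57 | 0.3, 8% | 0.6, 18% |
| 0.8 | 0.43 | 0.4, 15% | 0.8, 46% |

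Simulation of 3,000 trials per cell gave 5%, 7% and 15% for a 0.5-point shift, 9%, 18% and 46% for a 1-point shift, and about 5% with no shift. Against the 2-point target, the 1-point column is a bias of 20% to 40%.

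**Direction.** If controls report higher at baseline, or the experimental arm reports lower, s0 is negative and the experimental arm looks worse at month 6. The reverse makes it look better.

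**Shift that persists.** With a 1-point shift at both times and slope 0.6, net ANCOVA bias is 1 − 0.6 = 0.4, and the unadjusted bias is 1. A simulation at 149 per arm gave 0.41 and 1.01, with type I error of 11% and 30%. In general, if a fraction f of the baseline shift remains at month 6, ANCOVA has the smaller bias when |f − slope| < f, that is when f > slope/2; at slope 0.6 this means f above 0.3.

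**Dependence on the SD.** If the plan's calculation already allowed for the covariate, the implied SD at correlation 0.6 is 6.16 / √(1 − 0.36) = 7.7. The SE becomes 6.16 × √(2/149) = 0.71, and the 1-point error rate falls from 18% to about 13% (0.6 / 0.71 = 0.84 in the formula above). The bias in points does not change.

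**The case against.** The strongest reply is that nothing in the article shows a reaction to allocation. A reader might infer that participants certainly knew their arm when they answered. That is a strong inference, but it is not stated: unblinded describes the trial, not the date of disclosure, and the flowchart (Figure 1) was not available for this review. The shift, slope and SD are all assumed. This stands, and it is why the result is a range conditional on a shift and not an estimate of bias.

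A reader might also infer that adjusting for this score is simply wrong and that the covariate should be dropped. The arithmetic does not support that. Controls are still unblinded and still waiting at month 6, so a reporting shift may well persist, and then the unadjusted comparison can be the worse one.

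Computing the error rates with all 187 per arm, at slope 0.6, gives about 9% and 21%. That ignores the planned 20% dropout; with 149 analysed per arm they are about 8% and 18%.

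Two apparent safeguards fail. Requiring the adjusted and unadjusted estimates to agree in sign lowers the type I error only from 17.4% to 16.7% for a 1-point baseline-only shift in simulation, because both use the same month-6 data. Comparing baseline CUDIT-R by arm has power of about 11% to 12% for a 0.5-point shift and 29% to 35% for 1 point, and it cannot separate reaction from chance.

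What remains is the order of procedures. It is stated in the article, it is a design feature and not a detail left to an analysis plan, and both the primary model and the analysis set depend on it.

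**Conclusion.** The point holds in conditional form. As written, the covariate and the analysis-set condition both come from a self-reported survey sent after randomisation in an unblinded trial, with no statement that allocation was withheld. If allocation moved the baseline answers and the shift faded by month 6, a shift of 0.5 to 1 point would bias the primary effect by 0.2 to 0.8 points and raise type I error to between about 6% and 46%. This rests on an assumed slope of 0.4 to 0.8, a back-solved SD of 6.16, a two-sided test and 149 analysed per arm. Persistence to month 6 partly offsets the bias. The documents do not show that a shift occurred, or its direction. The effect of arm-related non-response cannot be sized from them. The sample size of 374 is not affected. The protocol should be changed, but this does not show the primary result to be invalid.

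**What to change.** 1. For anyone not yet randomised, release the REDCap randomisation only after the baseline survey has been submitted. This removes both routes for those participants.
2. For those already randomised, state when allocation was disclosed. If it was withheld until the survey was submitted, one sentence saying so settles the covariate question for them.
3. Keep the ANCOVA as primary. Pre-specify a sensitivity analysis of month-6 CUDIT-R by randomised arm in all randomised participants, whether or not they answered the baseline survey. Leave out baseline CUDIT-R and adjust only for variables confirmed to have been recorded before randomisation. This needs checking: Table 1 places sociodemographic data in the baseline survey, and Eligibility criteria documents only a threshold of monthly use, not a graded frequency.
4. Report both estimates with intervals. Do not add a joint success rule or rely on a baseline comparison by arm.

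The cost is an ordering rule in REDCap and one extra analysis. With no covariates its interval is wider than the ANCOVA interval by a factor of 1/√(1 − slope²): 1.09 at slope 0.4, 1.25 at 0.6 and 1.67 at 0.8. At SD 6.16 and 149 per arm it still has about the planned 80% power for 2 points.
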